### Criteria for discontinuation

Every effort will be made to retain patients in the trial and to minimise withdrawals. However, any severe or life-threatening event will be sufficient to remove a patient from the study. Failure of either procedure is likely to result in the patient being given a general anaesthetic and, hence, being withdrawn from the study. Patients may request to be withdrawn from this study at any time. Reasons for withdrawal will be documented. Intention to treat and “as treated” analyses will be performed.

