### Objectives and outcome measures

This study aims to compare local anaesthetic infiltration to a BPB anaesthetic technique for the surgical creation of an AVF, assessing in particular whether an increase in flow at the time of surgery with a BPB alters long-term outcome. The primary outcome measure is AVF primary patency at three months. Primary patency is defined as the unequivocal clinical presence of a thrill or audible bruit indicating flow through the fistula, in a fistula which has not required intervention to maintain or re-establish flow for whatever reason. Secondary outcomes include immediate post-operative patency (within one hour of termination of the procedure), primary patency at one month and one year, primary functional patency at three months and one year (that is, primary patency as described previously but which is also able to deliver flow greater than 350 ml/minutes without recirculation for the duration of haemodialysis), secondary patency at one year (that is, patency maintained by other therapeutic interventions, for example, interventional radiology), flow rates through AVF at one month, three months and one year, flow rates of the radial/brachial artery at one month, three months and one year measured by ultrasound, flow obtained at first HD, flow on HD after one year, change in cephalic vein diameter pre-/post-anaesthetic, change in radial or brachial artery flow pre-/post-anaesthetic, alteration of the surgical plan after anaesthetic and then venous/arterial mapping with ultrasound, AVF infection requiring antibiotics, pain during the procedure, pain one hour post-operatively, patient satisfaction, BPB success, complications including the requirement for conversion to general anaesthesia, the requirement for additional sedation or analgesics peri-operatively, post-operative paraesthesia or weakness suggestive of nerve damage, pneumothorax and time to perform the procedure.

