### Randomisation

A computer generated 1:1 allocation sequence (in random permuted blocks of either four or six) will be created by an independent operator who is not directly involved with the study. Allocation concealment will be achieved using sequentially numbered, sealed opaque envelopes. An intravenous cannula will be inserted and standard monitoring applied, and then based on the randomization, the anaesthetist will perform either an ultrasound guided BPB as necessary or ask the operating surgeon to undertake local anaesthetic infiltration.

Patients in the Ultrasound Guided BPB group will receive an ultrasound guided brachial plexus block. A supraclavicular block will be performed unless there is a contraindication, in which case an axillary block will be used. A 1:1 mixture of 0.5% L-bupivicaine and 1.5% lignocaine with adrenaline (1 in 200,000) will be injected, using a minimum of 25 mls and up to a volume of 40 ml [20]. Maximum dose limits of 2 mg/kg for bupivicaine and 7 mg/kg for lignocaine with adrenaline will be observed, recognising that these are additive. The time taken to perform the block and any technical problems during block insertion will be recorded in the patient’s case report file (intravascular puncture, paraesthesia). Measurements of the sensory block of the musculocutaneous, median, radial and ulnar nerves will be recorded every five minutes by a non-blinded observer using a previously validated 3-point scale using a cold test: 0 = no block, 1 = analgesia (can feel touch but not cold) and 2 = anaesthesia (patient cannot feel touch) [21]. Motor block of the musculocutaneous, median, radial and ulnar nerves will be graded using a previously validated scale as either 0 = no block, 1 = paresis, 2 = paralysis [21]. Measurements will be continued until either the sensory block is adequate in the operative area distribution or a maximum of 20 minutes has elapsed at which point the block will be supplemented by targeted axillary or midhumeral supplementation as appropriate using ultrasound. If a BPB block fails despite supplementation, LA infiltration will be used. This will be recorded as a failed block. If intravenous opioid analgesia is required for operative site discomfort, the BPB will be recorded as a failed block. Anaesthetists performing ultrasound guided BPBs in this study will have been deemed competent to perform this technique by the principle investigator.

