### Sample size and statistical considerations

Mean AVF failure after formation is reported to lie within the range 25 to 35% [4]. From our own retrospective audit data of patients receiving an ultrasound guided BPB over a two-year period, patients who had received BPB had an AVF survival rate of 93% compared with 52% in patients who received local anaesthetic infiltration [23]. In order to calculate sample size, we made the following assumptions: type 1 error (α) was set at 0.05 and Type 2 error (β) at 0.8. Therefore, if we assume a standard 65% AVF success rate overall, and propose that success rates with the use of BPB will be around 85%, then 57 patients are required in each group. In order to account for attrition of around 10%, we aim to recruit 126 patients. It should be noted that whilst these audit data were significantly in favour of the BPB, the data were retrospective, with non-standardised endpoints and also suffered from all the standard limitations of a retrospective analysis.

The null hypothesis (H0) for this study is that the use of ultrasound guided brachial plexus block does not reduce AVF primary failure rate when compared with local anaesthetic infiltration.

The study will be performed using both intention to treat and “as treated” analysis. In the intention to treat analysis, data will still be analysed from patients where the block has failed (that is if local anaesthetic supplementation is required), or if the patient was unable to receive randomised treatment for any other reason. In the “as treated” analysis, only data from patients completing randomised treatment will be analysed.

Secondary data analyses will be carried out on all secondary outcomes. These will be compared between groups using *t*-test and Mann–Whitney, or Chi-squared tests as appropriate.

It is anticipated that recruitment for this study will take up to two years to complete if one to two patients are enrolled each week. Data collection for each patient will occur during the operative and immediate post-operative period, and at dialysis sessions and post-operative follow-up as directed by the vascular team for one year.

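### The discontinuation rule may take patients out of the study for failed anaesthesia or a severe event, although the intention-to-treat analysis is defined to include them

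*Protocol article*

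**What the plan says.** The Protocol article deals with these patients in two places.

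- **Criteria for discontinuation.** On technique failure: "Failure of either procedure is likely to result in the patient being given a general anaesthetic and, hence, being withdrawn from the study". On safety: "any severe or life-threatening event will be sufficient to remove a patient from the study". The section then closes its account of withdrawals with "Intention to treat and “as treated” analyses will be performed".
- **Sample size and statistical considerations.** For a failed block, the rule under intention to treat reads: "data will still be analysed from patients where the block has failed (that is if local anaesthetic supplementation is required". A wider clause then takes in every remaining obstacle to the allocated technique: "or if the patient was unable to receive randomised treatment for any other reason". By contrast, for the as-treated analysis the rule is narrower: "only data from patients completing randomised treatment will be analysed".

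The primary outcome is primary patency at three months (Objectives and outcome measures). A blinded observer assesses it when patients attend routine clinics or dialysis (Postoperative management).

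On a failed block, the Randomisation section says: "If a BPB block fails despite supplementation, LA infiltration will be used". It has this recorded as a failed block and mentions neither general anaesthesia nor withdrawal.

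**The concern.** Conversion to general anaesthesia is a reason for not receiving the randomised treatment, so the intention-to-treat definition brings the patient in. The discontinuation section expects the same patient to leave the study. Conversion happens on the day of surgery and the primary outcome falls three months later. Intention to treat can use only outcomes that are collected, and the article does not say that they are collected after withdrawal.

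At stake is the comparability of the arms. Removal would happen after randomisation and would depend on how the allocated technique performed, so its frequency could differ between arms. It would also be decided with the allocation known, since the Blinding section accepts that patient and surgeon cannot be blinded. The Background says that general anaesthesia itself increases intra-operative vasodilatation, the mechanism by which the block is expected to help. Converted patients need not resemble the rest, and the direction of any bias cannot be predicted.

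**Working it through.** **1. The plan's own figure.** Inputs from Sample size and statistical considerations: 65% versus 85%, α = 0.05, and the stated 0.8 read as power. The pooled formula is

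n = [z(1−α)·√(2·p̄·(1−p̄)) + z(power)·√(p1(1−p1) + p2(1−p2))]² / (p2−p1)².

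With p̄ = 0.75 and a one-sided α this is (1.645·√0.375 + 0.842·√0.355)² / 0.04 = 56.9, hence 57 per arm, as stated. Adding 10% gives 114 × 1.10 = 125.4, hence 126, or 63 per arm. The point does not rest on an arithmetic error. (Sidedness is not stated; the two-sided version gives 73. That is a separate matter.)

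**2. Loss of power.** On the one-sided basis that reproduces 57, power is 83.5% with all 63 per arm observed, 81.8% if 5% of each arm is removed and 79.9% if 10% is removed. The two-sided values are 74.2%, 72.0% and 69.6%. The loss is modest.

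**3. Extreme bounds on the difference.** The article gives no conversion or removal rate, so 5% and 10% are assumptions. Let m of 63 be removed in each arm, with 65% and 85% patent among those observed. The difference among all randomised is lowest if every removed local anaesthetic patient is patent and every removed block patient is not, and highest in the reverse case:

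difference = 0.20·(63−m)/63 ± m/63.

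| Removed per arm | Observed patent, local / block | Lowest | Highest |
|---|---|---|---|
| 3 (5%) | 39/60, 51/60 | 51/63 − 42/63 = 14.3 points | 54/63 − 39/63 = 23.8 points |
| 6 (10%) | 37.05/57, 48.45/57 | (48.45 − 43.05)/63 = 8.6 points | (54.45 − 37.05)/63 = 27.6 points |

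The fractional counts only hold the rates at 65% and 85%. The planned difference is 20 points.

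**4. Milder scenarios.** Suppose there is no true effect, with 65% patent in both arms, and a fraction f of one arm is removed whose patency would have been q. That arm then shows (0.65 − f·q)/(1 − f), a distortion of f·(0.65 − q)/(1 − f). All values of f and q are assumptions.

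- f = 5%, q = 52%: (0.65 − 0.026)/0.95 = 65.7%, or +0.7 points.
- f = 10%, q = 40%: (0.65 − 0.04)/0.90 = 67.8%, or +2.8 points.
- f = 15%, q = 25%: (0.65 − 0.0375)/0.85 = 72.1%, or +7.1 points.
- q = 65%: no distortion at any f.

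If removed patients did better than the rest (q above 65%), the sign reverses.

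**The case against.** The best defence is that withdrawal here means leaving the allocated technique, with the statistical section governing the analysis. The discontinuation section opens by promising every effort to keep patients in, and it announces intention to treat in the same paragraph. The statistical section describes a year of data collection for each patient. Routine clinics, dialysis and the renal registry would make the outcome available. A loss of 10% is also what the sample size already allows for.

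Part of this stands. Removal is described as likely after technique failure and as permitted after a severe event, so it is not automatic. Loss of the three-month outcome is inferred and not stated. But the rule refers to the study, not to the technique, and uses the same word for patients who ask to leave. No sentence keeps either group in follow-up. The attrition allowance protects power; it does not protect against selective loss.

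Three stronger readings are tempting, and the article does not support them:

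- A reader might infer that removal hides safety outcomes. Adverse event reporting and safety has events followed until they resolve or stabilise, with no exception for withdrawn patients.
- A reader might infer that listing "complications including the requirement for conversion to general anaesthesia" as an outcome contradicts the rule. Conversion can be recorded when it occurs, and reasons for withdrawal are to be documented.
- A reader might infer that the two accounts of a failed block flatly contradict each other. Local infiltration may be the first step and general anaesthesia a later one. The text does not say so, which supports a request to reconcile them and no more.

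**Conclusion.** The point holds as a conflict within the current text. One section expects or permits removal from the study for technique failure with general anaesthesia, or for a severe event; another includes patients who could not receive their randomised treatment in the intention-to-treat analysis; neither says that follow-up continues. The consequence is a possible loss of primary outcomes and a possible bias, not a certain one.

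Its size is unknown because no conversion rate is given. The ranges of about 14 to 24 points (5% removed) and 9 to 28 points (10% removed) are extreme bounds that require opposite outcomes among the removed patients of the two arms. The one-arm scenarios run from 0.7 to 7.1 points, and to zero if removed patients resemble the rest. Selection matters more here than power. The wording should be settled while follow-up is still possible, because a blinded three-month examination that was not made cannot be made at the analysis stage.

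**What to change.** Amend Criteria for discontinuation so that conversion to general anaesthesia, or a severe event, is recorded as not completing the randomised technique. State that the patient remains in follow-up at 1, 3 and 12 months and is analysed in the arm randomised, and that follow-up ends only if consent to it is withdrawn. This concerns data collection alone and leaves clinical management untouched. The as-treated analysis is already limited to completers, so it needs no study withdrawal.

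Reconcile the Randomisation section and Criteria for discontinuation on what follows a failed block. Which management is right is not for this review to say.

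The cost is a short amendment and a few extra follow-up records. The target of 126 is unchanged, and the visits already use routine clinics, dialysis sessions and the renal registry.

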### Data collection

Data will be obtained from the anaesthetic record, recovery room observation chart, from clinical review in the post-operative period and from the electronic renal patient registry. Patient demographics, including age, gender, ethnicity, weight, body mass index and co-morbidities, as well as the surgeon, site of AVF (that is, distal or proximal arm), type of anastomosis (that is, end-to-side or side-to-side), duration of surgery, the type of anaesthesia used and fistula outcomes, will be recorded in the case report form. The researcher will be blinded to the technique used. Data will be anonymised. Case report files will be archived in a locked facility for a period of five years.

### Sample size and statistical considerations

Mean AVF failure after formation is reported to lie within the range 25 to 35% [4]. From our own retrospective audit data of patients receiving an ultrasound guided BPB over a two-year period, patients who had received BPB had an AVF survival rate of 93% compared with 52% in patients who received local anaesthetic infiltration [23]. In order to calculate sample size, we made the following assumptions: type 1 error (α) was set at 0.05 and Type 2 error (β) at 0.8. Therefore, if we assume a standard 65% AVF success rate overall, and propose that success rates with the use of BPB will be around 85%, then 57 patients are required in each group. In order to account for attrition of around 10%, we aim to recruit 126 patients. It should be noted that whilst these audit data were significantly in favour of the BPB, the data were retrospective, with non-standardised endpoints and also suffered from all the standard limitations of a retrospective analysis.

The null hypothesis (H0) for this study is that the use of ultrasound guided brachial plexus block does not reduce AVF primary failure rate when compared with local anaesthetic infiltration.

The study will be performed using both intention to treat and “as treated” analysis. In the intention to treat analysis, data will still be analysed from patients where the block has failed (that is if local anaesthetic supplementation is required), or if the patient was unable to receive randomised treatment for any other reason. In the “as treated” analysis, only data from patients completing randomised treatment will be analysed.

Secondary data analyses will be carried out on all secondary outcomes. These will be compared between groups using *t*-test and Mann–Whitney, or Chi-squared tests as appropriate.

It is anticipated that recruitment for this study will take up to two years to complete if one to two patients are enrolled each week. Data collection for each patient will occur during the operative and immediate post-operative period, and at dialysis sessions and post-operative follow-up as directed by the vascular team for one year.

We recognise that while this study is powered for the primary outcome, it is not powered for all the secondary outcomes. Whilst other studies suggest that our study is in fact overpowered for the secondary outcome of flow rate, this may not confer a clinical benefit, unlike our primary outcome, which is the reason this outcome has been selected. Any secondary data we collect in this study will provide useful information for further studies looking specifically at these outcomes.

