### Hypothesis

The creation of arteriovenous fistulae under ultrasound guided brachial plexus block anaesthesia will result in an increased primary patency rate at three months compared to the use of local anaesthetic infiltration.

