## Conclusions

The purpose of this trial is to investigate the hypothesis that long-term AVF patency is improved by a BPB compared to local anaesthetic infiltration as this has not yet been demonstrated in a large randomised controlled trial. Reducing the AVF failure rate is of significant benefit by increasing the number of patients able to commence HD when planned and reducing the number of “redo” procedures. This has clear financial benefits and also reduces the inconvenience to patients and the risks of further AVF surgery. If, however, our null hypothesis is correct, this finding would still provide useful information. LA infiltration is simpler, less time consuming and avoids the rare risks of brachial plexus blocks. LA infiltration also bypasses the financial and practical implications of requiring an anaesthetist to undertake the block, and monitor the patient. Therefore, either a positive or negative result will help inform future anaesthetic practice regarding the surgical creation of arteriovenous fistulae.

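### 57 per group gives 80% power only for a one-sided 5% test that the protocol never declares, and β is printed as 0.8 where 0.2 is meant

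*Protocol article*

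**What the plan says.** All the inputs stand in the protocol article under Sample size and statistical considerations. The error rates are given as "type 1 error (α) was set at 0.05 and Type 2 error (β) at 0.8". The control assumption is "if we assume a standard 65% AVF success rate overall", and the calculation ends with "propose that success rates with the use of BPB will be around 85%, then 57 patients are required in each group". Allowing for roughly 10% attrition, the target is 126 patients, or 63 per group under 1:1 allocation. The same section later says "We recognise that while this study is powered for the primary outcome".

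Nowhere does the article say whether the 5% level is one- or two-sided. It does word its hypotheses in one direction. The Hypothesis section expects that the block "will result in an increased primary patency rate at three months compared to the use of local anaesthetic infiltration", the last paragraph of the Background says much the same, and the null hypothesis is that the block "does not reduce AVF primary failure rate when compared with local anaesthetic infiltration".

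**The concern.** Two things do not fit.

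- **The printed β.** A type 2 error of 0.8 is 20% power. No trial is planned on that basis, and it does not lead to 57 per group.
- **The sample size itself.** When α = 0.05 is given without qualification, most readers take it as two-sided. On that reading, 57 per group is too few for 80% power at 65% against 85%.

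The claim of adequate power for the primary outcome therefore depends on something the article does not state. Undeclared sidedness also leaves a choice that could be made after the data are seen. Some plausible results would be positive on one reading and negative on the other.

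**Working it through.** **Inputs, all from the sample size section.** p1 = 0.65 (control), p2 = 0.85 (block), d = 0.20, α = 0.05, intended power 0.80, n = 57 per group. Then:

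- mean proportion p̄ = 0.75, so √(2p̄q̄) = √0.375 = 0.6124
- √(p1q1 + p2q2) = √(0.2275 + 0.1275) = √0.355 = 0.5958

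**Formula (pooled variance under the null, no continuity correction).** n = [z_α√(2p̄q̄) + z_β√(p1q1 + p2q2)]² / d²

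**Reproducing the plan's figure, one-sided 5%, power 0.80.** (1.645 × 0.6124 + 0.842 × 0.5958)² / 0.04 = (1.007 + 0.501)² / 0.04 = 56.9, so **57 per group**. This matches.

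**Two-sided 5%, power 0.80.** (1.960 × 0.6124 + 0.842 × 0.5958)² / 0.04 = (1.200 + 0.501)² / 0.04 = 72.4, so **73 per group**.

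**Could another standard method explain 57 as two-sided?**

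| Method | One-sided | Two-sided |
|---|---|---|
| Pooled | 57 | 73 |
| Unpooled | 55 | 70 |
| Arcsine | 56 | 71 |
| Pooled, continuity-corrected | 67 | 83 |

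No two-sided version comes below 70. Reading the 65% as the average of both arms (45% against 85%) gives 17 one-sided or 22 two-sided, so that does not explain 57 either.

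**The printed β taken literally.** Power 0.20 at two-sided 5% gives (1.200 − 0.501)² / 0.04 = 12.2, so 13 per group. The 57 was not computed that way.

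**Power for 65% against 85%.** Power = Φ[(d√n − z_α√(2p̄q̄)) / √(p1q1 + p2q2)]

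- One-sided, n = 57: (1.510 − 1.007) / 0.5958 = 0.844, power 80.1%
- Two-sided, n = 57: (1.510 − 1.200) / 0.5958 = 0.520, power **69.8%**
- Two-sided, n = 63 (no attrition): (1.587 − 1.200) / 0.5958 = 0.650, power **74.2%**

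Exact binomial enumeration agrees. Two-sided at 57 per arm, power is 71.0% for the uncorrected chi-squared test and 63.4% for Fisher's test. At 63 per arm the figures are 75.0% and 68.4%. The one-sided uncorrected test at 57 per arm has 80.7%.

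**Where sidedness decides the result.** Suppose 37 of 57 control fistulae (65%) are patent.

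| Block arm | Difference | One-sided p | Two-sided p |
|---|---|---|---|
| 45/57 | 8/57 = 14 points | 0.048 | 0.095 |
| 46/57 | 9/57 = 16 points | 0.029 | 0.058 |

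The p values are from the uncorrected test.

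**Attrition.** 57 × 1.1 = 62.7, so 63 per group and 126 in total. After 10% loss, 126 × 0.9 = 113.4 remain, against 114 needed. That step is close enough and is not part of this point.

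**The case against.** The strongest reply is that nothing is miscalculated. The study hypothesis and the null both run in one direction, and 57 is exactly what a one-sided calculation gives. The sample size then agrees with the stated hypotheses, and the claim of adequate power is true for the matching test. On this view the 70% figure applies only to an analysis the article never commits to, and the β is a harmless slip.

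Much of this stands. The article does not promise a two-sided test, so a reader who concludes that the trial is simply underpowered goes beyond the text. But a directional hypothesis does not declare a one-sided test, since directional hypotheses are routinely tested two-sided. Nor is this a detail that can be left to an unseen analysis plan: the article itself prints α, β, both rates and n, and they do not agree on the ordinary reading of α = 0.05. The β is wrong on any reading, although 57 shows that power 0.8 was used.

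Two further inferences are tempting and not supported:

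- That the primary test must be two-sided because chi-squared is the test named for binary data. The article names its tests only for secondary outcomes, and the primary test may be given elsewhere.
- That the Conclusions equate a non-significant result with a true null. The sentence is conditional: "If, however, our null hypothesis is correct, this finding would still provide useful information". It sets no such rule and claims no equivalence.

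**Conclusion.** The point holds as an internal disagreement among the stated design figures. β = 0.8 is an error for β = 0.2. The 57 per group delivers 80% power only for a one-sided 5% test, which the hypotheses allow but the article does not declare. If the primary test is two-sided at 5%, the chance of missing the planned 20-point benefit is about 30% with 57 evaluable per arm and about 26% with 63, instead of 20%. If it is one-sided, the 80% stands, but the false-positive allowance in the favoured direction is 5%, twice the 2.5% of a two-sided 5% test.

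This rests on taking 65% as the control rate and on the article's own rates of 65% and 85%. The two-sided power figures use the uncorrected normal approximation, which the exact chi-squared calculation supports to within about a percentage point. Fisher's test would be lower.

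**What to change.** Keep the 126 patients and change the sample size section as follows:

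1. Replace the printed type 2 error with β = 0.2 (power 0.8).
2. Declare, before analysis, whether the primary comparison is one- or two-sided.
3. State the matching power for 65% against 85%. If one-sided at 0.05, this is 80% with 57 evaluable per arm, with the 5% false-positive allowance in the favoured direction stated openly. If two-sided at 0.05, it is about 70% with 57 per arm and about 74% with 63.
4. Qualify the later statement that the study is powered for the primary outcome to match.

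This costs wording only. The price is either a less favourable stated power or an openly declared one-sided 5% test. Restoring 80% two-sided power would instead take 73 / 0.9 = 81.1, so 82 per group and 164 in total. The fix does not require that.

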## Background

When chronic kidney disease (CKD) progresses to irreversible end stage renal failure, renal replacement therapy (RRT) is necessary for survival [1]. Haemodialysis (HD) is the commonest form of RRT. Good quality, stable vascular access is a major factor in determining survival in this group of CKD patients, and surgical creation of an arteriovenous fistula (AVF) is recommended as the optimal technique [2,3]. Unfortunately, approximately one-third of arteriovenous fistulae fail at an early stage [4]. This failure rate is influenced by both the pre-operative arterial and venous diameters and post-operative flow through the AVF, as well as a number of other patient and surgical factors [5,6]. Some anaesthetic techniques can directly influence venous diameter as well as intra- and post-operative blood flow [5], but there is no conclusive evidence as yet that any particular anaesthetic technique can significantly influence long term surgical outcome.

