Patients in the Local Anaesthetic Infiltration group will receive infiltration of local anaesthetic into the surgical site by the operating surgeon under sterile conditions using a combination of 0.5% L-bupivicaine prior to incision and 1% lignocaine topically after the wound is opened. Maximum dose limits of 2 mg/kg for bupivicaine, and 3 mg/kg for lignocaine will be observed, recognising that these are additive.

Using the technique described above, at the points marked on the skin the internal diameters of the cephalic and basilic veins will again be measured. Because after a successful BPB patients will generally have an immobile, vasodilated, warm arm, blinding from this stage will be difficult. The average of three measurements at each position will again be calculated. Similarly, the arterial blood flow will be measured by Doppler ultrasound as described previously, and again the average of three measurements will be recorded. The veins and artery at the proposed surgical site will also be examined and mapped using ultrasound by the surgeon. The operating surgeon will use this information to decide on the final site for the fistula. Any deviation from the pre-operative plan based on anatomical information obtained using ultrasound at this stage will be recorded.

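### Pre/post vessel outcomes are set for unadjusted tests although their baselines are measured; ANCOVA on baseline and planned artery would be more precise, and any site adjustment must use the planned site

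*Protocol article*

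**What the plan says.** All places are in the protocol article.

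- **Outcomes.** Objectives and outcome measures lists among the secondary outcomes "change in cephalic vein diameter pre-/post-anaesthetic, change in radial or brachial artery flow pre-/post-anaesthetic".
- **Tests.** Sample size and statistical considerations assigns t-test, Mann–Whitney "or Chi-squared tests as appropriate" to the secondary outcomes. It names no covariate, and it names no test for three-month primary patency.
- **Baseline data.** Pre-operative management has a blinded observer measure vein diameters and arterial flow before the anaesthetic, each as the mean of three readings. Flow is taken in whichever of the two arteries is intended for the fistula.
- **Site.** The Randomisation section repeats the measurements after the anaesthetic, and the surgeon then maps the vessels: "The operating surgeon will use this information to decide on the final site for the fistula". Departures from the pre-operative plan are recorded. Data collection lists the fistula site without saying whether it is planned or final.
- **Allocation.** The Randomisation section gives "A computer generated 1:1 allocation sequence (in random permuted blocks of either four or six" and names no stratification factor.
- **Prognosis.** Background says of fistula failure: "This failure rate is influenced by both the pre-operative arterial and venous diameters and post-operative flow through the AVF".

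**The concern.** A t-test on a change score fixes the coefficient of the baseline at 1. ANCOVA estimates it and so gives a smaller variance unless the true slope happens to be 1. The flow outcome also covers two arteries in one measure, so differences between arteries enter the residual variance unless the artery is in the model. These two outcomes carry the mechanistic argument of the trial, that the block dilates vessels and raises flow, so the precision is worth having.

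The second risk concerns site. The surgeon chooses the final site after seeing what the anaesthetic did to the vessels, and a change of surgical plan is itself a listed outcome. An analyst who adjusts or subgroups by final site would condition on a consequence of treatment and could remove part of the effect under study.

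**Working it through.** **1. The plan's own figure.** The plan states 65% against 85% success, "type 1 error (α) was set at 0.05 and Type 2 error (β) at 0.8" (read as power 0.80), and "then 57 patients are required in each group".

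n = [z_α√(2p̄q̄) + z_β√(p₁q₁+p₂q₂)]² / δ², with p̄ = 0.75, √0.375 = 0.612, p₁q₁+p₂q₂ = 0.2275 + 0.1275 = 0.355, √0.355 = 0.596, δ = 0.20.

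- One-sided: (1.645×0.612 + 0.842×0.596)²/0.04 = 56.9, so 57. This reproduces the plan.
- Two-sided: (1.960×0.612 + 0.842×0.596)²/0.04 = 72.4, so 73. At 57 per group, two-sided power is about 70%.

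This is background for step 4 only.

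**2. Change score against ANCOVA, equal variances.** Let σ² be the variance before and after, and ρ the within-arm correlation between them. The documents give no ρ, so it is assumed.

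- Change score: 2σ²(1−ρ)
- ANCOVA: σ²(1−ρ²)
- Ratio: (1−ρ²)/[2(1−ρ)] = (1+ρ)/2

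| assumed ρ | ratio | reduction | 57 per group with ANCOVA is worth, on change scores |
|---|---|---|---|
| 0.5 | 0.75 | 25% | 57/0.75 = 76 |
| 0.7 | 0.85 | 15% | 57/0.85 ≈ 67 |

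**3. Unequal variances.** Let k be the pre-anaesthetic SD divided by the post-anaesthetic SD. The ratio becomes (1−ρ²)/(1+k²−2ρk) = (1−ρ²)/[(1−ρ²)+(k−ρ)²]. This never exceeds 1. It equals (1+ρ)/2 at k = 1, and there is no gain at k = ρ. With k = 0.8 as an illustration (assumed):

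- ρ = 0.5: 0.75/0.84 = 0.89
- ρ = 0.7: 0.51/0.52 = 0.98

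The gain can therefore be much smaller if the anaesthetic widens the spread, but ANCOVA does not lose to the change score beyond the one or two degrees of freedom it uses out of 114 − 2 = 112.

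**4. Primary patency.** Expected failures at 57 per group: 57×0.35 + 57×0.15 = 28.5. A simulation (4,000 runs per row) held the marginal rates at 65% and 85%, with an assumed 50:50 site mix and one standardised baseline measure. It compared the unadjusted z-test with logistic regression. The variance ratio refers to the standardised risk difference, and power to a two-sided test of the treatment effect.

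| assumed site OR / OR per SD | variance ratio | power unadjusted | power adjusted |
|---|---|---|---|
| 1 / 1 | 1.02 | 72% | 70% |
| 1.5 / 1.25 | 0.99 | 71% | 71% |
| 2 / 1.5 | 0.96 | 72% | 73% |
| 3 / 2 | 0.89 | 72% | 75% |

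Two-sided type I error stayed between about 4.5% and 5% with and without adjustment.

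**The case against.** The strongest reply is that nothing here is an error. Unadjusted tests after unstratified blocked randomisation are valid, covariates are commonly left to a statistical analysis plan that is not shown, and the two outcomes are secondary. The equal-variance formula is also doubtful if the block dilates vessels. Validity stands in full, and so does the caution on size, which step 3 quantifies. What remains is that the article does assign tests to the secondary outcomes, and it defines these two as changes from a measured baseline.

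Four stronger readings are tempting, and the documents do not support them.

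- **That primary patency is to be analysed unadjusted.** The named tests refer to secondary outcomes, and no primary test is stated.
- **That adjustment is free precision.** The documents give no prognostic strength. Background names vessel diameters and post-operative flow, not fistula site, and step 4 shows a small loss when the covariates do not predict. Vessels under 1.8 mm are excluded, which may also narrow the prognostic range.
- **That lack of stratification exposes the primary result.** With an assumed 50:50 mix, the 95% limit of chance imbalance is 1.96√(2×0.25/57) = 18 points. An assumed 30-point site effect turns that into 5.5 points. But this is the edge of the range, and it already sits inside the ordinary standard error, whose 95% half-width is 1.96√(0.355/57) = 15 points.
- **That the case report form holds the final site, or that planned site is a listed field.** Data collection does not say which site is recorded. Planned site is only implied, by the artery chosen for baseline flow and by the recording of deviations.

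**Conclusion.** The point holds as an efficiency and pre-specification recommendation, firmest for the two pre/post vessel outcomes. There the named tests leave out a baseline that the trial measures. The gain is 25% of the variance at ρ = 0.5 and 15% at ρ = 0.7. It rests on assumed correlations and equal variances, and it shrinks if the post-anaesthetic spread is larger.

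The warning about site rests on the document's own order of events: the final site is decided after the anaesthetic, so only the planned site is a safe covariate or subgroup factor.

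For primary patency, adjustment is optional. Its effect is about −2 to +4 power points on assumed prognostic strengths. With about 28 failures there is room for one or two covariates, and no adjustment in this range closes the gap between 57 and 73 per group.

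**What to change.** 1. Analyse post-anaesthetic vein diameter and arterial flow by ANCOVA, with the pre-anaesthetic value and the planned artery as covariates. Report the adjusted mean difference with a 95% CI.
2. State that any adjustment or subgroup by site, including for primary patency, uses the planned pre-operative site and not the final site. Label the two separately in the case report form.
3. If primary patency is to be adjusted, pre-specify this before the data are examined. Limit it to planned site, baseline cephalic vein diameter, or both, and report a risk difference standardised from the logistic model with its 95% CI, because the adjusted odds ratio is a different, conditional quantity.

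The cost is wording, one clear field label and slightly more analysis. The baseline measurements are already planned, and the planned artery should be recoverable from where baseline flow was measured.
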